## Abstract

Background

Median sternotomy in cardiac surgery is associated with severe pain, and opioid-based analgesia is currently standard. In recent years, various ultrasound-guided nerve block types have been used in cardiac surgery to reduce opioid use and facilitate postoperative recovery, including ultrasound-guided transversus thoracic muscle plane block. However, the 90% effective concentration of ropivacaine used for ultrasound-guided transverse thoracic muscle plane block (TTPB) in cardiac surgery remains undetermined. This study aims to evaluate the 90% effective concentration of ropivacaine for ultrasound-guided transversus thoracic muscle plane block in adult cardiac surgery using the biased coin up-and-down sequential method.

Methods

This study is a single-center, prospective, sequential allocation dose-finding trial. Participants will be adult patients with American Society of Anesthesiologists physical status (ASA-PS) II-IV undergoing elective cardiac surgery with median sternotomy. Ultrasound-guided transversus thoracic muscle plane block will be performed after induction of general anesthesia at 0.4 ml.kg^-1^ ropivacaine per side (0.8 ml.kg^-1^ bilaterally), with concentrations pre-determined by biased coin up-and-down sequential method. Successful transversus thoracic muscle plane block is to be defined as less than a 20% increase in heart rate or blood pressure from the baseline value within one minute after the skin incision in the midline of the chest. The 90% effective concentration of ropivacaine will be estimated using isotonic regression.

Conclusions

The results of this study will help establish guidelines for transversus thoracic muscle plane block in cardiac surgery and may facilitate the optimization of healthcare resources.

## Introduction

Background and rationale

Good perioperative pain management affects patient recovery and quality of life, especially in cardiac surgery. Median sternotomy is known to be extremely painful and systemic administration of opioids has traditionally been used for perioperative analgesia [1,2]. However, this method carries side effects, such as severe constipation, nausea and vomiting, respiratory depression, prolonged intubation periods, and hyperalgesia [3]. Insufficient management can lead to chronic pain at the wound site, which reduces the patient’s postoperative outcome and quality of life [1,2]. Therefore, multimodal perioperative analgesia, including non-narcotic analgesics and regional anesthesia, is important. Among regional anesthesia, neuraxial anesthesia (such as epidural anesthesia) is also an effective option for perioperative analgesia after thoracic surgery, but in cardiac surgery, the increased risk of epidural hematoma due to systemic heparin administration during surgery is a concern [2,4].

In recent years, with the improvement of ultrasound-guided regional anesthesia techniques, various nerve blocks have been used for perioperative pain management following cardiac surgery [5-8]. Ultrasound-guided transverse thoracic muscle plane block (TTPB) is an ultrasound-guided nerve block that was first reported in 2015 [9,10]. In TTPB, local anesthetic is injected into the fascial plane between the transverse thoracic muscle and the internal intercostal muscles to provide analgesia in the anterior cutaneous branch region of the intercostal nerves (T2-6) in the anterior chest, making it effective for wound pain following median sternotomy and reducing the need for opioids [9-12]. Other chest wall blocks reported for cardiac surgery include the pectoral nerve (PECS) block and the parasternal intercostal block (PIPB) [5,13]. The analgesic coverage of the PECS block is limited to the lateral chest wall and is not suitable for analgesia during median sternotomy [5]. The PIPB targets the anterior branches of the intercostal nerves by injecting local anesthetic into the fascia between the pectoralis major and external intercostal muscles, making it effective for median sternotomy analgesia [13]. However, it may provide inadequate blockage of the medial branches of the intercostal nerves and requires puncture of multiple intercostal spaces [13]. In contrast, unlike PIPB, TTPB can cover analgesia for median sternotomy incisions with a single intercostal puncture [13]. However, reports of TTPB as an analgesic strategy for adult cardiac surgery featuring median sternotomy do not currently feature guidelines on establishing the ideal concentration and dose of ropivacaine.

Objectives

The primary objective of this study is to determine the concentration of ropivacaine that provides effective analgesia in 90% of adult cardiac surgery patients (90% effective concentration: EC90) undergoing median sternotomy with ultrasound-guided TTPB. The effectiveness of TTPB at the start of surgery will be evaluated using the change in hemodynamics during skin incision as an index of noxious stimulation.

Trial design

This single-center, prospective, interventional, sequential allocation dose-finding study, using the biased coin up-and-down design targeting EC90, is designed to determine the optimal concentration of ropivacaine for ultrasound-guided TTPB during adult cardiac surgery.

## Materials and methods

Study setting

The trial will be conducted by the Department of Anesthesiology within the University of Tsukuba Hospital.

Eligibility criteria

The following inclusion (Table 1) and exclusion criteria (Table 2) will be applied to all potential enrollees.

**Table 1 TAB1:** Inclusion criteria.

Inclusion criteria
Patients undergoing cardiac surgery via median sternotomy
ASA-PS (American Society of Anaesthesiologists physical status classification) II - IV
Patients aged 18 to 80 years at the time of informed consent

**Table 2 TAB2:** Exclusion criteria.

Exclusion criteria
History of median sternotomy
Malformation, nerve damage or infection near the nerve block puncture site
History of allergies to local anaesthetics or drugs used for general anaesthesia
Pregnant
New York Heart Association functional classification Class IV symptomatic heart failure
Pulmonary hypertension requiring inhaled nitric oxide
Preoperative artificial ventilation management
Severe blood coagulation disorder
A serious systemic illness
Cases of infective endocarditis
Patients taking drugs that inhibit cytochrome P450 1A2 (CYP1A2)
Patients who are deemed inappropriate by the principal investigator (or sub-investigator)

Intervention description

General anesthesia will be induced as required for adult cardiac surgery. Ultrasound-guided TTPB is to be performed after oral tracheal intubation. Before ultrasound-guided TTPB, the anatomy of the puncture site (bilateral parasternal region) will be confirmed using a linear probe with an effective frequency range of 4-18 MHz and a center frequency of 10 MHz (L18-4, Konica Minolta, Tokyo, Japan) on an ultrasound device (SONIMAGE HS2, Konica Minolta, Tokyo, Japan). For ultrasound-guided TTPB, the ultrasound probe is to be placed parallel to the ribs at the 4th/5th intercostal space 1 cm lateral to the sternal edge, and the internal intercostal muscles, transverse thoracic muscles, and pleura must be clearly identified before puncture is then performed using a 22G block needle in the parallel technique. After confirming that the block needle has advanced to the transverse thoracic fascia surface, 3 ml of saline will be test-injected per side to confirm hydro-dissection of the transverse thoracic fascia surface. Then, ropivacaine (Anapeine, Sandoz Pharma K.K., Tokyo, Japan) will be administered at 0.4 ml.kg^-1^ on one side (0.8 ml.kg^-1^ on both sides). The concentration of ropivacaine used in TTPB is to be determined in advance using a biased coin designed up-and-down method (BC-UDM) [14-16]. The maximum dose of ropivacaine was set at 300 mg in accordance with the package insert for Japanese ropivacaine formulations. Based on this, the maximum tolerated dose of ropivacaine in BC-UDM was set at 3.2 mg.kg^-1^ (ropivacaine concentration 0.4%). An experienced anesthesiologist will administer the above treatment. The image displayed on the ultrasound device during injection will be printed out, and an image evaluator can then judge whether the local anesthetic has been properly injected into the transverse thoracic fascia. After TTPB, a central venous catheter and (if necessary) a pulmonary artery catheter are to be placed. A post-scan will then be performed using an ultrasound device in the parasternal region to confirm that the local anesthetic has spread to the transverse thoracic fascia surface in the parasternal region in the T2-6 range. After the block, patients will be monitored with electrocardiography and invasive arterial pressure measurement. A 20% fat emulsion will be kept readily available in the operating room. In the event of systemic toxicity, lipid therapy will be initiated with a 1.5 mL/kg bolus of 20% fat emulsion, repeated as necessary, followed by a continuous infusion at 0.25 mL/kg/min. In cases of severe circulatory instability, extracorporeal circulation will be established immediately in cooperation with the cardiac surgery team. Surgery will be started at least 20 minutes after TTPB, and the effectiveness of TTPB will be evaluated when making an incision in the skin in the midline of the chest.

Permitted care

General anesthesia will be induced by intravenous injection of midazolam, remimazolam, or propofol, and inhalation of 1-5% sevoflurane. After muscle relaxation is achieved by intravenous injection of 0.6-1.0 mg.kg^-1^ rocuronium, remifentanil will be administered continuously at 0.2-0.4 µg.kg^-1^.min^-1^ for about 5 minutes, followed by oral tracheal intubation. The maintenance concentration of sevoflurane after tracheal intubation will be adjusted to an exhaled concentration of 1-1.5%. The continuous administration of remifentanil will be discontinued after disinfection of the surgical field, and no additional administration is to be given until median sternotomy. Before the start of surgery, the state of muscle relaxation will be evaluated using a train-of-four (TOF) monitor. If the TOF is 1 or higher, an additional 10-20 mg of rocuronium is to be administered. The effectiveness of TTPB will be assessed during the period from the skin incision at the start of surgery to the median sternotomy. Sympathetic nervous responses (heart rate and blood pressure) were evaluated as indicators of noxious stimulation. If the blood pressure or heart rate increases by 20% or more from the baseline value measured at the end of the induction of anesthesia within 1 minute after the skin incision in the midline of the chest, it will be judged as failed TTPB and, if the increase is less than 20%, it will be judged as successful TTPB [17-20]. If the ultrasound-guided TTPB block is unsuccessful, a bolus of 0.1-0.2 µg.kg^-1^ of remifentanil will be administered immediately as a rescue. After efficacy assessment of TTPB, there are no restrictions on remifentanil or fentanyl and any administration will occur at the discretion of the attending anesthesiologist. After intubation, the ventilator settings will be set to FIO2 0.4, and the inspiratory pressure and ventilation rate will be adjusted in pressure-controlled mode to achieve an exhaled carbon dioxide of 35-40 mmHg.

Prohibited care

Ropivacaine is metabolized by the hepatic enzyme CYP1A2. Because this may potentially affect the results of the study, patients using the drugs that have a CYP1A2 inhibitory effect (vemurafenib and anastrozole used within four weeks prior to surgery, and other drugs used within one week prior to surgery) will be excluded from the study, and use of such concomitant drugs is not permitted under this protocol (Table 3).

**Table 3 TAB3:** List of prohibited drugs during this trial.

Common name	Drug Category Name	Japanese Product Name
Famotidine	H2 receptor antagonists	Gaster
Ticlopidine	Antiplatelet agents	Panaldine
Ciprofloxacin	New quinolone antibacterial agents	Ciproxan
Norfloxacin	New quinolone antibacterial agents	Baccidal
Pazufloxacin	New quinolone antibacterial agents	Pasil, Pazucross
Vemurafenib	Anticancer drugs (BRAF inhibitors)	Zelboraf
Anastrozole	Aromatase inhibitors for postmenopausal breast cancer treatment	Arimidex
Allopurinol	Hyperuricemia treatment	Zyloric
Stiripentol	Antiepileptic drugs	Diacomit
Fluvoxamine Maleate	Selective serotonin reuptake inhibitors (SSRIs)	Depromel, Lubox
Disulfiram	Anti-alcoholism drugs	Nocbin
Methylthioninium chloride hydrate	Treatment for methemoglobinemia	Methylene blue
Fomepizole	Ethylene glycol/methanol poisoning agent	Fomepizole
Deferasirox	Iron chelators	Jadenu
Ritrecitinib Tosilate	Disease-modifying antirheumatic drugs (Janus kinase inhibitors)	Litfulo

Outcomes

Primary Outcome

The primary outcome of this study is the EC90 of ropivacaine for use in ultrasound-guided TTPB, calculated from the success or failure of ultrasound-guided TTPB at the start of cardiac surgery via median sternotomy. Changes in heart rate and blood pressure were used to assess nociceptive responses. A ≥20% increase from the baseline value within 1 minute after the midline chest incision indicated an unsuccessful TTPB, while a <20% increase indicated success [17-20].

Secondary Outcomes

The need for additional narcotics (fentanyl, remifentanil) between skin incision at the start of surgery and median sternotomy will be evaluated.

Harms

Anticipated adverse events include: 1) Local anesthetic toxicity: Severe local anesthetic toxicity of convulsions or worse occurs at a frequency of 2.6/10,000 with ultrasound-guided nerve blocks [21]. 2) Tissue damage due to puncture: pneumothorax (frequency of occurrence is 4/10,000 with ultrasound-guided nerve blocks) [21,22], vascular damage, cardiac damage. 3) Nerve damage due to puncture (frequency of occurrence is 4/10,000 with ultrasound-guided nerve blocks) [21,23]. 4) Infection at the puncture site.

Complications due to the puncture are assessed by post-procedure scanning with an ultrasound device and observation in the surgical field. Complications due to drug administration are assessed based on changes in vital signs. The content, extent, treatment, outcome, and severity of the complications are recorded in the medical record and case report, and follow-up surveys are conducted if necessary (those due to the administration of general anesthesia are not covered). If an adverse event occurs, medically necessary treatment and care will be provided under the guidelines of national health insurance, even after the completion of the trial.

Participant timeline

The timeline of participants is shown in the table below (Table 4).

**Table 4 TAB4:** The participant timeline. X indicates timing of enrolment, intervention, and assessments. - indicates not applicable.

	Screening Period	Study Period				
Time point	From surgery decision to the day before surgery	On the day of surgery				The day after surgery
		Anesthesia induction	Skin incision	Median sternotomy	End of surgery	
Obtaining consent	X	-	-	-	-	-
Eligibility screen	X	-	-	-	-	-
Registration	X	-	-	-	-	-
Check vital signs	X	X	X	X	X	X
Ultrasound pre-scan of the puncture site	-	X	-	-	-	-
Intervention (transversus thoracic muscle plane block)	-	X	-	-	-	-
Ultrasound post-scan of the puncture site	-	X	-	-	-	-
Check for muscle relaxation	-	X	-	-	-	-
Primary outcome	-	-	X	-	-	-
Secondary outcome	-	-	-	X	-	-
Check for postoperative surgical site infection	-	-	-	-	-	X
Check for postoperative pneumonia	-	-	-	-	-	X
Safety assessment	X	X	X	X	X	X

Sample size

A stopping rule is necessary in dose-finding studies based on a BC-UDM [15]. A minimum sample size of n = 50-60 is recommended for calculating EC90 [14]. The stopping rule is set at 45 successful blocks [16]. The target sample size is thus 70 cases, with an estimated dropout rate of 10%.

Recruitment

Prior to the day of surgery, researchers will review the medical records of patients scheduled for surgery and determine potential participants based on the inclusion and exclusion criteria. Researchers will then visit the patients and ask them to participate in the study.

Assignment of interventions: allocation

In the first case, 0.2% ropivacaine is used. In subsequent cases, the concentration of ropivacaine is to be determined based on the success or failure of the previous block according to a BC-UDM (Figure 1) [14-16]. For the calculation of EC90, if the previous block was unsuccessful, the next higher concentration (increased or decreased by 0.025%) is to be used, and if the block was successful, there is an 8/9 chance of using the same concentration and a 1/9 chance of using the next lower concentration. The floor dose of ropivacaine is 0.1% and the ceiling dose is 0.4%. If the floor dose of 0.1% ropivacaine is successful, the next patient will be assigned to the same concentration (0.1%) and, if the ceiling dose of 0.4% ropivacaine is unsuccessful, the next patient will be assigned to the same concentration (0.4%). Randomization of successful blocks is to be performed using computer-generated random numbers. The patients are to be registered after obtaining consent. The biostatistician of the study will create the random allocation sequence and communicate it by email to the researcher (YN) in charge of allocation. YN will then enroll and allocate participants.

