**Figure 1 FIG1:**
[figure not shown]
Flow chart of allocation procedure.

Blinding

The researcher who will not perform TTPB is informed of the allocation and will have the local anesthetic prepared outside the operating room before the patient enters the room. The concentration of the local anesthetic is not to be written on the syringe so that study participants and the researcher who will perform TTPB (KT) will be blinded to the ropivacaine concentration.

The researcher performing the TTPB and blinded to the concentration of ropivacaine (KT) will assess whether the TTPB is successful or not, and will collect data at the start of surgery. Another member of the research group who is not blinded to the concentration of ropivacaine (MO) will collect the remaining perioperative data.

Data collection

Research data for this study will be collected from electronic medical record systems or case report forms (CRFs). Preoperative data, including demographics, medical history, medication history, laboratory test results, and preoperative evaluations, will be completed on a CRF by the investigator prior to surgery.

Data management

All data will be anonymized and CRFs and electronic data will be coded with a subject identification code. Electronic data recording media and paper documents will be stored on lockable shelves in a lockable room and kept locked at all times. Deleted information, etc., will be stored in a file/folder separate from the analysis data with a password and managed by the principal researcher. As this is personal information, it will be recorded as an electronic file using a computer that is not connected to the Internet and will be password-locked on recording media outside the computer.

Statistical methods

Primary Outcome

The EC90 is defined as the dose of ropivacaine at which successful block was observed in 90% of patients in the study population. EC90 will be calculated using isotonic regression [14-16]. The estimator to be used for isotonic regression is the adjusted success rate of block at each concentration, estimated by the pooled-adjacent-violators algorithm (PAVA) [15,16]. The 90% confidence interval for the isotonic regression estimate of EC90 (Û3) is to be calculated using the bias-corrected percentile method using 2000 bootstrap replicates of Û3 [15,16]. All statistical analyses will be conducted with R version 4.5.0 or later (R Core Team, Vienna, Austria).

Secondary Outcomes

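### The 3.2 mg/kg (0.4%) ceiling is derived from a 300 mg maximum but respects it only up to 93.75 kg, and nothing limits weight or volume above that.

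*Protocol article*

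**What the plan says.** All of the relevant rules are in the Materials and methods of the protocol article.

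- **Absolute limit** (Intervention description): "The maximum dose of ropivacaine was set at 300 mg in accordance with the package insert".
- **Ceiling derived from it** (same paragraph): "Based on this, the maximum tolerated dose of ropivacaine in BC-UDM was set at 3.2 mg.kg^-1^ (ropivacaine concentration 0.4"%).
- **Volume** (same paragraph): ropivacaine "will be administered at 0.4 ml.kg^-1^ on one side (0.8 ml.kg^-1^ on both sides"). No upper limit in ml is given.
- **Allocation** (Assignment of interventions): "The floor dose of ropivacaine is 0.1% and the ceiling dose is 0.4"%, in steps of 0.025% from a 0.2% start. The next level depends only on the previous patient's result and the biased coin. A failure at 0.4% keeps the next patient at 0.4%.
- **Eligibility** (Tables 1 and 2): neither table has a weight or BMI criterion. The nearest item is exclusion at the investigator's discretion.
- **Blinding**: participants and the researcher who performs the block "will be blinded to the ropivacaine concentration", and that researcher also judges success.

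**The concern.** A per-kilogram ceiling can honour an absolute milligram limit only up to some body weight. The article presents the 3.2 mg/kg ceiling as following from the 300 mg maximum, but it names no reference weight and has no rule for heavier patients. For such a patient at a high level, three stated requirements cannot all be met: the 300 mg maximum, the fixed 0.8 ml/kg, and the allocated concentration.

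The main stake is safety. Local anesthetic toxicity is the first anticipated harm under Harms. The Discussion notes that chest wall blocks absorb local anesthetic faster than blocks elsewhere, and gives lower toxicity risk as a reason for the study.

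A second stake is conditional. Staff who try to respect 300 mg are not told whether to reduce volume or concentration, and concentration is the quantity the trial estimates.

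**Working it through.** **Inputs from the article:** 300 mg maximum; 0.8 ml/kg in total; levels 0.1% to 0.4% in steps of 0.025%; start at 0.2%; step down with probability 1/9 after a success; stop at 45 successes; target of 70 cases.

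**1. The plan's own figure.** 0.4% is 4 mg/ml, and 4 mg/ml × 0.8 ml/kg = 3.2 mg/kg. This reproduces the stated ceiling exactly.

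**2. Weight at which each level reaches 300 mg.** Weight = 300 / (concentration in % × 10 × 0.8).

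| Level | mg/kg | Weight at 300 mg | Dose at 100 kg | Dose at 120 kg |
|---|---|---|---|---|
| 0.4% | 3.2 | 93.75 kg | 320 mg | 384 mg |
| 0.375% | 3.0 | 100 kg | 300 mg | 360 mg |
| 0.35% | 2.8 | 107.1 kg | 280 mg | 336 mg |
| 0.325% | 2.6 | 115.4 kg | 260 mg | 312 mg |
| 0.3% | 2.4 | 125 kg | 240 mg | 288 mg |
| 0.2% (start) | 1.6 | 187.5 kg | 160 mg | 192 mg |

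At 0.4% the excess is 20 mg at 100 kg (20/300 = 7%) and 84 mg at 120 kg (84/300 = 28%).

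**3. How often this would arise.** The ceiling is (0.4 − 0.2)/0.025 = 8 net steps above the start. The article gives neither the true EC90 nor patient weights, so the frequency was simulated from the stated rule with 4,000 runs per setting. The assumptions, none of them from the article, are:

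- the trial stops at 45 successes or 70 patients;
- the response curve is logistic with slope 20 or 40 per 1% concentration;
- weights are normal with mean/SD 62/12, 68/14 or 75/16 kg, which puts 0.4%, 3.3% or 12% of patients above 93.75 kg.

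| True EC90 | Mean patients at 0.4%, any weight | Expected patients over 300 mg | Chance of at least one |
|---|---|---|---|
| 0.25% or less | 0 | at most about 0.01 | about 1% or less |
| 0.30% | about 0.1 or less | 0.001–0.19 | 0.1–16% |
| 0.35% | 3.4–3.8 | 0.02–1.7 | 2–77% |
| 0.40% | 19–32 | 0.09–4.9 | 9–99% |

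The upper ends come from the heaviest weight distribution. With 68/14 kg the expected number is about 0.02 at an EC90 of 0.30%, 0.23–0.32 at 0.35% and 0.8–1.2 at 0.40%. With 62/12 kg it never exceeds 0.15.

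**4. Volume that holds 300 mg.** At 0.4%: 300/4 = 75 ml in total, 37.5 ml per side. If volume were cut only when the limit is exceeded, a 120 kg patient would receive 300/4 = 75 ml at 0.4%, 300/3.75 = 80 ml at 0.375%, 300/3.5 = 85.7 ml at 0.35%, 300/3.25 = 92.3 ml at 0.325%, and the full 120 × 0.8 = 96 ml at 0.3% or below. In such a patient the volume would reveal the concentration.

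**The case against.** The strongest reply is that no stated number is wrong. The 3.2 mg/kg figure reproduces, and the 300 mg sentence carries no weight condition, so it can be read as binding every patient. On that reading, 384 mg at 120 kg would breach the text, and what is missing is only a preparation detail that an article may leave to the full protocol. This reading is possible, but it does not resolve the conflict. The article also states a fixed ml/kg volume without a cap and an allocation that ignores weight. With 300 mg as an overriding cap, one of those two must still give way, and the article does not say which. The conflict lies between rules that are printed, so it is more than an omission.

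The reply is right on several other matters. The frequency rests on assumed weights and an unknown EC90, and may be close to zero. No effect on the EC90 is established: cutting volume leaves the recorded concentration correct, and only unrecorded dilution would place a patient at the wrong level. An experienced operator, invasive pressure monitoring, lipid rescue, extracorporeal support and discretionary exclusion all reduce the risk, although none is a weight rule. A uniform volume cap also reduces volume at low concentrations, where 300 mg is not threatened. That last cost is real and is accepted below to protect blinding.

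**Conclusion.** The concern holds. The stated ceiling keeps the adopted maximum only up to 93.75 kg at 0.4%, 100 kg at 0.375%, 107 kg at 0.35% and 115 kg at 0.325%. This part is exact and needs no assumption.

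The practical impact is small unless the sequence climbs to about 0.35% or above; how small depends on the assumed weights and curves. The true EC90 is what the trial sets out to find, and 0.4% is a level the design allows, so a safety limit should hold over the whole permitted range. The point should be fixed before more patients are dosed at the upper levels. It is a safety inconsistency and does not show that the primary estimate is biased.

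**What to change.** State in both the Intervention description and the allocation section that the 300 mg total overrides, and hold it in a way that leaves the allocated concentration unchanged. Suggested wording: *Volume is 0.4 ml/kg per side, with dosing weight capped at 93.75 kg (37.5 ml per side, 75 ml in total) at every concentration.* The alternative is to limit enrolment to 93.75 kg or less.

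The same cap should apply at all levels. A cut made only when 300 mg is exceeded would let the volume disclose the concentration to the blinded operator who judges success.

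If a patient's concentration is nevertheless diluted, analyse that patient at the concentration actually injected, and do not let the result drive the next allocation as though the assigned level had been given.

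**Cost:** one sentence in each of two sections. Under the cap, patients above 93.75 kg receive less than 0.8 ml/kg even at low concentrations: 75/100 = 0.75 ml/kg at 100 kg and 75/120 = 0.625 ml/kg at 120 kg. Under the weight limit they are excluded, which narrows the study population slightly.

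### Surgical site infection and pneumonia are checked once, on the day after surgery, so a zero count would mean only that none was seen by then

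*Protocol article*

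**What the plan says.** The Harms section of the protocol article lists four groups of anticipated events: local anesthetic toxicity, tissue damage (pneumothorax, vascular, cardiac), nerve damage, and "Infection at the puncture site". It gives rates for severe toxicity, pneumothorax and nerve damage, but none for infection.

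On detection it states: "Complications due to the puncture are assessed by post-procedure scanning with an ultrasound device and observation in the surgical field". Drug-related complications are judged from vital signs. Complications are recorded with their treatment and outcome, with further follow-up where needed; no trigger or end date is given.

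Table 4 (Participant timeline) ends with the column "The day after surgery". The rows "Check for postoperative surgical site infection" and "Check for postoperative pneumonia" are marked in that column alone. The row "Safety assessment" is marked at every time point and also ends there.

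The Data collection section names electronic medical record systems as a data source, alongside case report forms.

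**The concern.** For infection, the schedule does not fit the harms list. Infection at the puncture site is anticipated, but the two methods named for puncture complications are applied on the day of surgery, and the only scheduled infection check comes one day later. An infection that becomes apparent after that check has no planned route into the data. The same holds for pneumonia, which the sponsor chose to record.

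What is at stake is how a count is read. A report of no infections and no pneumonia could be taken as reassurance about the technique, when the data would support only the statement that none was seen by the day after surgery.

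**Working it through.** The protocol states no figure that depends on the length of harms follow-up, so there is nothing to reproduce. The check is a comparison of sections, followed by simple binomial arithmetic.

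**1. Harms against stated detection**

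| Event | In the Harms list | Stated method | Last scheduled look |
|---|---|---|---|
| Local anesthetic toxicity | yes | vital signs | day after surgery |
| Pneumothorax, vascular, cardiac damage | yes | post-scan, surgical field | methods on day of surgery; general safety assessment to next day |
| Infection at the puncture site | yes, no rate | post-scan, surgical field; nearest Table 4 row is surgical site infection | one check, day after surgery |
| Pneumonia | no | Table 4 row only | one check, day after surgery |

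The early harms fall within the period observed. Infection is the listed harm that can develop after the last scheduled look.

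**2. What a zero count can exclude**

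Inputs: n = 70 (the target in Sample size); n = 50 (lower end of the recommended minimum in the same section); n = 56 (50/0.9 = 55.6, rounded up, using the stated 10% dropout). For zero events the one-sided 95% upper limit is 1 − 0.05^(1/n):

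- n = 70: 1 − 0.05^(1/70) = 4.2%
- n = 56: 1 − 0.05^(1/56) = 5.2% (rule of three: 3/56 = 5.4%)
- n = 50: 1 − 0.05^(1/50) = 5.8% (rule of three: 3/50 = 6.0%)

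These limits reflect sample size. They bound the risk of an event that is visible by the day after surgery, and say nothing directly about later onset.

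**3. How much the window might matter (assumed values only)**

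Let r be the true incidence and s the share of cases apparent by the day after surgery. The documents give neither. Assume r from 1% to 10% and s from 5% to 25%. In 70 patients:

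- Cases in total, 70 × r: 0.7 to 7. Chance of at least one, 1 − (1 − r)^70: 50.5% to 99.9%.
- Cases found by the next-day check, 70 × r × s: 70 × 0.01 × 0.05 = 0.035, to 70 × 0.10 × 0.25 = 1.75. Chance of at least one, 1 − (1 − rs)^70: 3.4% to 83%.

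Under the same assumption on s, zero events in 70 would bound the full-course risk only at 4.2%/s, which is 4.2%/0.25 = 17% or 4.2%/0.05 = 84%. The spread is so wide that no size for the undercount can be claimed.

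**The case against.** The strongest reply has four parts.

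- **Onset times are not in the documents.** That some infections appear after the first day is general clinical knowledge, and the assumed ranges run from a 3.4% to an 83% chance of seeing a case. This stands: a near-certain zero cannot be claimed, nor any particular undercount.
- **Further follow-up is provided for, and this is a condensed article.** The clause exists, and its trigger and duration may be in a fuller protocol. But it follows the sentence on recording treatment and outcome, so it reads as following complications already found. Table 4 is a schedule that the article does state.
- **The trial makes no claim about infection.** Its safety argument in the Discussion concerns local anesthetic toxicity, and harms are neither a primary nor a secondary outcome. This stands, and keeps the point modest.
- **There is no comparator.** Every patient has both the block and a sternotomy, so a longer count could not be attributed to the block. This also stands. It limits what the count can show, but does not make a one-day count complete.

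A reader might go further and infer that the listed harms in general will be recorded as absent, or that nerve injury is missed because follow-up is short. The documents do not support either. Toxicity, pneumothorax, vascular and cardiac damage are covered by monitoring, scan and surgical view. For nerve damage, the protocol's own 4/10,000 gives 70 × 0.0004 = 0.028 expected cases and a 1 − (1 − 0.0004)^70 = 2.8% chance of any, so a zero is likely whatever the window. Nor do the documents say that patients are still sedated on the day after surgery. Pneumonia is a Table 4 row and not a listed harm.

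**Conclusion.** The point holds for infection as a listed harm, and for pneumonia as an item the sponsor chose to collect. Each has a single scheduled check on the day after surgery and no defined later window, so later cases would be missed. A zero count supports only a bound on risk to that day: about 4.2% in 70 patients, 5% to 6% in 50 to 56.

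This rests on one assumption from outside the documents, that some infections appear after the first day. The size of the undercount cannot be derived from what is given. The EC90, its estimator and the stopping rule are unaffected. This is an inexpensive improvement to harms reporting and no defect in the primary analysis.

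**What to change.** Extend the surgical site infection and pneumonia rows of Table 4 to hospital discharge, read from the electronic medical record that Data collection already names. Report each count with its observation window and an upper 95% confidence limit. If the schedule stays as it is, state in the report that the counts cover events seen by the day after surgery and should not be read as absence of the harm.

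The cost is one additional column in Table 4, one chart review per patient and slightly later data completion, with no extra visit or bedside examination. The longer count would still be descriptive: with no comparator, events could not be attributed to the block or to a ropivacaine concentration.
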